#### **Treatment allocation**

Treatment allocation will be done according to the usual delivery process. After randomization, the investigator is responsible for completing the randomization list and the accountability documents to record reception of study product.

## **7.8 Study Procedures: visits, sampling and evaluated parameters**

### **7.8.1 Study visits**

There will be 6 study visits:

- V1: Screening and enrolment visit
- V2: Treatment start
- V3 and V4: Treatment period
- V5: Follow up visit 72 hours after treatment initiation
- V6: Outcome visit at Day 28 ±7 days after randomization

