### 3 Study Flow Chart

#### STUDY FLOW CHART

| Study Periods                                           | Screening & Enrolment | Treatment start | oXiris™ Treatment period 48hrs (2x24h) | Toraymyxin™ and/or SOC Treatment period (2x2h and/or SOC) | Follow up 72hrs | Outcome D28 ± 7days |
|----------------------------------------------------------------|----------------------------------|------------------------|-----------------------------------------------|------------------------------------------------------------------|------------------------|----------------------------|
| Study visits                                            | V1                        | V2              | V3+ V4                                 | V3+ V4                                                    | V5              | V6                  |
| Procedures                                              |                                  |                        |                                               |                                                                  |                        |                            |
| Demographics                                                   | x                                |                        |                                               |                                                                  |                        |                            |
| Medical History                                                | x                                |                        |                                               |                                                                  |                        |                            |
| Infection site, type of infection, documented microbial agents | x                                |                        |                                               |                                                                  |                        |                            |
| Antibiotic therapy                                             | x                                |                        |                                               |                                                                  |                        |                            |

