### **6.4 Secondary endpoints**

The secondary endpoints are the following:

- Measurement of IL-6 and HMGB1 T0 i.e. patient inclusion, at T24 hours, T48 hours, and T 72 hours after treatment initiation;
- Routine measurements of norepinephrine dose, inotropic score, and vasopressor dependency index T0, T24, T48 and T72;
- Haemodynamics: MAP, CVP, HR, CO, ELWI, PVPI T0, T24, T48 and T72
- Routine measurements of volume requirement T0, T24, T48 and T72;
- Routine measurements of ventilation parameters PO2/FiO2, SvO2 T0, T24, T48 and T72;
- Urine output (ml/d)
- Lactate, procalcitonin and pH measurements at T0, T24, T48 and T72 after treatment initiation;
- SOFA score calculation at T0, T24, T48 and T72 ;
- Incidence of renal failure, ICU length of stay
- Patient survival at D28;
- Recording of AEs/SAEs

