## **7.7 Assignment to study treatment**

#### **Randomization**

All eligible patients will be randomly assign to either conventional SOC treatment according to the Surviving Sepsis Campaign Guidelines (27), or SOC treatment with oXiris™ hemofiltration, or SOC treatment with Toraymyxin™ hemoperfusion within 24 hours of admission to the ICU. Patients will be distributed into these 3 groups, in accordance with the randomization table kept in the investigator's office. The randomization list will be performed using a computer generated (simple random number) scheme.

The allocation sequence is concealed in sealed envelopes held at the study centre, which is available 24 hours a day.

According to paragraph 7.5.1 withdrawn patients will be replaced in order to analyse 10 patients per group.

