#### 7.9.5 Visit 6: Outcome

- Discharge from ICU
- Discharge from hospital
- Survival 28 days  $\pm$  7 days after randomization. Patients will be contacted by phone, if the patient is no longer in hospital. In case, documented attempts to contact the patient have failed, a rapid contact with the patient's general practitioner will be initiated. To be in line with the data protection requirements the patients gives the consent to contact the general practitioner in the informed consent form. Date of death (if applicable)
- AE/SAE

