## **8.2 Foreseeable Adverse Events and Adverse Events related to Clinical Outcomes**

All Adverse Events (AE) will be collected during study days 0 to 28 (or until death).

The following events will be considered as clinical outcomes:

- Death related to septic shock, that is, related to septic shock or a sequel of sepsis based on the interpretation of the investigator
- Cardiovascular events: the need for vasoactive drugs or hypotension.
- Respiratory events: decreased PaO2/FiO2 mechanical ventilation, hypoxia, acute respiratory distress syndrome, acute lung injury or respiratory failure
- Hepatic events: hepatic injury or liver dysfunction that leads to an increase from baseline in the serum level of bilirubin
- Hematologic/coagulation events: coagulopathy, disseminated intravascular coagulation, thrombocytopenia or thrombocytosis
- Systemic inflammatory response related criteria: tachypnoea, hypopnoea, leucocytosis, leucopenia, hypothermia, hyperthermia, tachycardia and bradycardia

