### **8.3 Recording Procedures**

Clinical investigators and ultimately the Principal Investigator (PI) have the primary responsibility for AE identification and documentation,

All adverse events and adverse device effects should be documented. Depending on the nature of the event the reporting procedures below should be followed. Any questions concerning adverse event reporting should be directed to the Principal Investigator in the first instance.

The investigator is responsible for reporting all (S)AEs occurring during the course of the study. AEs (serious or non-serious) observed by the investigator and/or reported by the subject must be recorded in the patient file and subsequently in the CRF, i.e. the period of time from the first (= signature of informed consent and/or the presumed will of the participant) to the last protocol-specific procedure (Visit 6 on Day 28 or date of death) regardless of the study product relation assessment.

All observed or volunteered adverse device events (serious or non-serious) and abnormal test findings, regardless of treatment group or suspected causal relationship to the investigational device or study treatment(s) will be recorded.

AEs or abnormal test findings felt to be associated with the study treatment(s) will be followed until the event (or its sequelae) or the abnormal test finding resolves or stabilizes at a level acceptable to the investigator.

All AEs, serious and non-serious, will be fully documented in the appropriate CRF. For each AE, the investigator will provide the onset, duration, intensity, treatment required, outcome and action taken with the investigational product.

For all AEs, sufficient information will be pursued and/or obtained so as to permit an adequate determination of the outcome of the event (i.e., whether the event should be classified as a SAE) and an assessment of the causal relationship between the AE and the investigational study treatment.

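### The visit that establishes day-28 survival and closes adverse-event follow-up may take place from day 21, with no re-check at day 28, so a discharged patient phoned on days 21 to 27 has unknown day-28 status.

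*Protocol*

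**What the plan says.** Section 6.4 of the protocol lists "Patient survival at D28" among the secondary endpoints, with no window attached; the Synopsis does the same.

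The visit that supplies this endpoint is V6. Section 7.8.1 schedules it as "V6: Outcome visit at Day 28 ±7 days after randomization", and the flow chart in Section 3 heads the column "Outcome D28 ± 7days". In Section 7.9.5 the survival item itself carries the window: survival is recorded at 28 days plus or minus "7 days after randomization. Patients will be contacted by phone, if the patient is no longer in hospital". If documented attempts to reach the patient fail, the general practitioner is approached. The same visit records "Date of death (if applicable") and adverse events, and the flow chart places the study termination form there.

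The safety sections use a fixed end point. Section 8.2 states: "All Adverse Events (AE) will be collected during study days 0 to 28 (or until death"). Section 8.3 describes the last protocol procedure as "Visit 6 on Day 28 or date of death", without a window.

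The preceding scheduled visit is V5 at 72 hours. The protocol does not ask for another contact when V6 takes place before day 28.

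**The concern.** The endpoint is a status on a fixed day, but the contact that establishes it may come up to seven days too early. A patient who has left hospital and answers the telephone on day 21 is known to be alive on day 21. Nothing scheduled afterwards shows whether that patient was alive on day 28, or what adverse events occurred in the last week. The termination form completed at V6 can close the record at that moment.

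This is a rule for collecting data, so the analysis cannot repair it. A statistical analysis plan could specify that such patients count as alive, are censored or are treated as missing, but it cannot supply an observation that was never made. The only mortality endpoint would then mix statuses read at different times, and adverse-event follow-up would differ in length between patients. Section 13 gives the purpose of the pilot as providing data for the design of later studies; a day-28 event rate with a blurred time point serves that purpose less well.

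**Working it through.** **The window.** 28 − 7 = day 21 and 28 + 7 = day 35, so two patients' follow-up can differ by up to 14 days while both comply with the protocol.

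**The sections compared.**

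| Section | Content | Time point |
|---|---|---|
| 6.4, Synopsis | survival endpoint | day 28 |
| 3, 7.8.1, 7.9.5 | V6, survival reading | day 21 to day 35 |
| 8.2 | adverse-event collection | days 0 to 28, or death |
| 8.3 | V6 as last procedure | day 28 |

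A V6 on days 21 to 27 satisfies the second row and cannot by itself deliver the first, third or fourth.

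**Which contacts matter.**
- Contact on or after day 28: the date of death is recorded, so status at day 28 follows exactly.
- Contact on days 21 to 27, patient still in hospital: status at day 28 can be read from the hospital record.
- Contact on days 21 to 27, patient discharged: status at day 28 is unknown.

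**Possible size.** The protocol states no mortality rate and no figure to reproduce. The number of patients is 30, from Section 7.7 ("withdrawn patients will be replaced in order to analyse 10 patients per group", three groups). Everything else here is an assumption.

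Let m be 28-day mortality, assumed to be 20% to 50%. Take S(t) = exp(−H·(t/28)^k) with H = −ln(1 − m). Use k = 1 for a constant hazard and k = 0.5 for deaths concentrated early.

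*Extreme case: every visit on day 21 and nothing learned later.* Expected missed deaths = 30 × [S(21) − S(28)].

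- m = 20%, k = 0.5: S(21) = 0.8^(0.75^0.5) = 0.8243; 0.8243 − 0.8 = 0.0243; × 30 = 0.73.
- m = 50%, k = 1: S(21) = 0.5^0.75 = 0.5946; 0.5946 − 0.5 = 0.0946; × 30 = 2.84.

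*Visits spread evenly over days 21 to 35.* Expected missed deaths = 30 × (1/14) × the integral from 21 to 28 of [S(v) − S(28)] dv. For m = 50%, k = 1, the mean of S over days 21 to 28 is 0.0946 / (0.6931 × 7/28) = 0.546. The excess over 0.5 is 0.046; half the visits fall before day 28, so 30 × 0.5 × 0.046 = 0.69.

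| Assumed 28-day mortality | k | Dying between days 21 and 28 | Missed of 30, all visits on day 21 | Missed of 30, even spread |
|---|---|---|---|---|
| 20% | 1 | 4.6% | 1.38 | 0.34 |
| 20% | 0.5 | 2.4% | 0.73 | 0.18 |
| 30% | 1 | 6.5% | 1.96 | 0.48 |
| 30% | 0.5 | 3.4% | 1.03 | 0.25 |
| 40% | 1 | 8.2% | 2.45 | 0.60 |
| 40% | 0.5 | 4.3% | 1.28 | 0.31 |
| 50% | 1 | 9.5% | 2.84 | 0.69 |
| 50% | 0.5 | 4.9% | 1.46 | 0.35 |

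Per group of 10 this is 0.18/3 = 0.06 to 0.69/3 = 0.23 deaths under an even spread, and 0.73/3 = 0.24 to 2.84/3 = 0.95 in the extreme case. Both columns treat every patient's status as depending on the V6 contact. Deaths in hospital would be known anyway, so for given visit dates and mortality the figures err on the high side.

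**The case against.** The best defence is that the protocol fixes the endpoint at day 28, fixes adverse-event collection at days 0 to 28, and names V6 as falling on day 28 in Section 8.3. On that reading the seven days are ordinary scheduling tolerance, and what remains is loose wording. Section 8.3 also makes the investigator responsible for all adverse events during the study, whatever the date of the visit. Much of this stands. It does not help the discharged patient phoned early, because Section 7.9.5 applies the window to the survival reading and no section requires a further call.

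Four stronger readings are tempting, and the protocol supports none of them.

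- **Patients contacted early are counted as 28-day survivors.** No section says so. They might be censored, treated as missing or looked up again, and that rule could properly sit in an analysis plan that is not shown. They may be counted as survivors; that is as far as the text goes.
- **Deaths on days 29 to 35 become day-28 deaths.** The date of death is collected, so they need not be.
- **Contact timing will differ by arm because the trial is open.** This is possible, but nothing in the protocol suggests it.
- **The adverse-event period is cut by a quarter.** 7/28 = 25% describes one patient seen on day 21 about whom nothing is recorded afterwards. The stated period is still 28 days.

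**Conclusion.** The point holds for discharged patients contacted on days 21 to 27, and for them only. Their day-28 vital status is unknown and their adverse-event record incomplete, and Sections 8.2 and 8.3 disagree with the window in Sections 3, 7.8.1 and 7.9.5.

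Under assumed 28-day mortality of 20% to 50%, the expected loss is less than one death in the whole trial if visits are spread evenly. It approaches three only at the top of the assumed range with every visit on day 21. These numbers rest on the assumed mortality, the two hazard shapes and the assumed visit dates, none of which the protocol provides.

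Severity is minor. The primary endpoint, endotoxin activity at 72 hours, is untouched, and the endpoint affected is one of many secondary ones in a 30-patient pilot. The reason to act is that the gap is avoidable and cannot be closed at the analysis stage.

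**What to change.** - Set the V6 window to day 28 to day 35 after randomisation, with no V6 contact before day 28.
- State that survival is classified from the date of death relative to randomisation: dead if death occurred on or before day 28, otherwise alive at day 28.
- Count adverse events to day 28 for every patient, whenever V6 takes place.
- Use the same wording in the flow chart and in Sections 7.8.1, 7.9.5, 8.2 and 8.3.
- For patients already contacted before day 28, obtain day-28 status from the hospital record or through the general practitioner; Section 7.9.5 says the consent form covers that contact.

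For every patient reached under this rule, misclassification due to visit timing falls to zero. The cost is a short amendment, a contact window of 7 days in place of 14, somewhat later calls for some patients and a few look-ups. No visit is added.

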## **7.8.2 Sampling schedule**

### **7.8.2.1 Endotoxin measurements**

Endotoxin activity (EAA) will routinely be measured for patients admitted to the ICU if the diagnosis of Septic Shock is considered. Is the EAA level above the cut off threshold value 0.6 an evaluation for the study inclusion will be done (the result can be used for screening and enrolment (V1)). Furthermore the EAA will be measured at treatment start (V2), 24 hours after treatment initiation (V3), 48 hours after treatment initiation (V4), and 72 hours (V5) after treatment initiation (see treatment schedule p. 8). Blood samples will be obtained through an arterial line.

### **7.8.2.2 Cytokine and HMGB1 measurements**

IL-6 and HMGB1 will be measured at treatment start (V2), 24 hours after treatment initiation (V3), 48 hours after treatment initiation (V4), and 72 hours (V5) after treatment initiation (see treatment schedule p. 8). Blood samples will be obtained through an arterial, peripheral or central venous line. IL-6 and HMGB1 will be also measured in the effluent line in order to get information about the adsorption by the oXiris™ filter.

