### **7.6.3 oXiris™ treatment group**

#### Vascular access

In the oXiris™ group, patients will receive extracorporeal therapy over a venous double-lumen catheter, inserted through the jugular, subclavian or femoral vein. The catheter will be inserted by a trained physician according the guidelines for performing ultrasound guided vascular cannulation (28).

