#### Study treatment duration

The oXiris™ treatment will be applied during 48 hours of treatment i.e. two (2) oXiris™ sets each one used for 24 hours.

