#### oXiris™ set change

The oXiris™ set will be changed every 24 hours. The filter change should be done within a 30-45 min time frame.

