#### Treatment parameters

Mode: CVVHDF: 20% diffusion-80% convection

Dose: 35 ml/h/kg\*

Reinfusion: 50% Predilution, 50% Postdilution

Blood flow rate (Qb): 150 ml/min at least.

Filtration Fraction should be inferior to 15%.

Once hemodynamic stabilization is achieved, fluid overload should be managed according to the patient clinical needs.

\*prescribed dose to secure a delivered dose of min 25ml/h/kg

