### **7.8.2.4 Sampling recommendations**

Sampling, handling and storage details will be described in more detail in a study specific procedure and presented during the study training.

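### IL-6, HMGB1, lactate and procalcitonin have no fixed blood sampling site, so a central venous draw near a running circuit return can read low at T24 and T48, mainly in the oXiris arm

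*Protocol*

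**What the plan says.** Section 7.8.2.1 fixes the site for endotoxin activity: "Blood samples will be obtained through an arterial line". Section 7.8.3.1 repeats this. For IL-6 and HMGB1, section 7.8.2.2 has "Blood samples will be obtained through an arterial, peripheral or central venous line", and section 7.8.2.3 says the same for lactate and procalcitonin. All four markers are secondary endpoints in section 6.4, at T0, T24, T48 and T72. The CRF items in sections 7.9.1 to 7.9.4 do not include the sampling site. Section 7.8.2.4 adds: "Sampling, handling and storage details will be described in more detail in a study specific procedure".

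Under Vascular access in section 7.6.3, oXiris treatment runs "over a venous double-lumen catheter, inserted through the jugular, subclavian or femoral vein". Section 7.6.4 gives the same access for Toraymyxin. On duration, section 7.6.3 says: "The oXiris™ treatment will be applied during 48 hours of treatment i.e. two (2) oXiris™ sets each one used for 24 hours". On the daily change of set it says: "The filter change should be done within a 30-45 min time frame". The treatment parameters include "Reinfusion: 50% Predilution, 50% Postdilution".

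**The concern.** The oXiris circuit is meant to clear some of the substances being measured. Blood leaving the filter carries less of them than blood entering it, and it goes back into a large vein. A central venous sample taken downstream of that return, while the pump runs, is partly filter-outlet blood. It understates the systemic level, in the direction of apparent benefit. An arterial sample is taken after full mixing, so it keeps any true systemic fall and excludes this local effect.

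Central venous sampling is a realistic choice: CVP and SvO2 are recorded from Visit 2 to Visit 5, so a central line is likely to be in place. The trial is open, has 10 analysed patients per arm, and lets the site differ between patients and visits. The site is not among the listed CRF items, so an affected value could not be recognised afterwards. Section 7.8.2.2 also uses effluent IL-6 and HMGB1 to learn about adsorption, and interpreting those values needs a sound blood concentration.

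**Working it through.** The protocol gives no figure for this effect, so there is nothing to reproduce. The scale can be checked with a mixing model.

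**Formula.** Relative under-reading = f × E, where f is the share of circuit-return blood in the sample and E is the single-pass extraction. For a freely filtered solute, E = effluent / (inflow + predilution flow). This assumes neutral fluid balance and no solute in the fluids.

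**Inputs from section 7.6.3.** Prescribed dose 35 ml/h/kg; 80% convection; half of the reinfusion before the filter; blood flow at least 150 ml/min; filtration fraction below 15%.

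**Assumed.** Weight 70 kg, haematocrit 0.30, f from 5% to 50%.

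**A. Blood flow at its stated minimum.**
- Effluent = 35 × 70 / 60 = 40.8 ml/min.
- Ultrafiltrate = 0.8 × 40.8 = 32.7 ml/min; predilution = 32.7 / 2 = 16.3 ml/min.
- Plasma inflow = 150 × 0.70 = 105 ml/min.
- E = 40.8 / (105 + 16.3) = 34% on plasma flow, or 40.8 / (150 + 16.3) = 25% on whole-blood flow.

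**B. Is A compatible with the 15% limit?** The protocol does not define the filtration fraction.
- All ultrafiltrate over inflow plus predilution: 32.7 / 121.3 = 27% on plasma flow, or 32.7 / 166.3 = 20% on blood flow. Both exceed 15%, so under this definition the settings in A could not apply together. Since 150 ml/min is only a minimum, this is not a contradiction in the protocol.
- Postdilution share only: 16.3 / 121.3 = about 13%, so the limit does not bind.

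**C. Ceiling under the first definition.** Effluent = ultrafiltrate / 0.80, so E is at most 0.15 / 0.80 = 18.75%, at any weight. This holds when E and the filtration fraction use the same flow basis.

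**D. Under-reading, f × E, for a freely filtered solute**

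| Share of return blood, f (assumed) | E = 18.75% (C) | E = 34% (A) |
|---|---|---|
| 5% | 0.9% | 1.7% |
| 30% | 5.6% | about 10% |
| 50% | 9.4% | about 17% |

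For IL-6, HMGB1 and procalcitonin the documents give no single-pass extraction in patients. With an assumed E of 5 to 40%, the result is 0.2 to 2% at f = 5% and 1.5 to 12% at f = 30%. The 66% in section 5.1.1 cannot serve as E: it is endotoxin removed from recirculated bovine plasma over one hour.

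**E. Which arms, and when.**
- *oXiris:* assigned to every patient from 0 to 48 h. T24 falls at the set change and T48 at the end of treatment, so the circuit may or may not be running at the draw. The protocol does not say.
- *Toraymyxin:* same veins, with the second two-hour session about 24 h after initiation (section 7.6.4).
- *Ordinary CRRT:* allowed in any group (section 7.6.5). If the roughly 50% in section 5.1.3 held for the 20 SOC and Toraymyxin patients, about 20 × 0.5 = 10 would have such a circuit at some time. How many would be running at T24 or T48 is not given.

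**The case against.** The strongest reply is that section 7.8.2.4 defers sampling detail to a procedure that is not at hand and that may settle site, lumen and timing. That limits certainty about practice. It does not change the protocol's own text, which expressly permits all three sites.

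A second reply is that the effect needs several things at once: a central venous draw, close to the return, with the pump running. Arterial and peripheral samples are free of it, as are samples taken during a set change or after disconnection. Femoral return with upper-body sampling makes it unlikely. This stands, and it makes the typical effect small.

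A reader might infer three stronger things, none of which the documents support.
- *A bias confined to the oXiris arm.* Sections 7.6.4 and 7.6.5 allow circuits in the other arms. An imbalance remains, because oXiris is assigned for 48 h while CRRT elsewhere depends on need, and section 7.2.2 describes Toraymyxin as selective for endotoxin (although section 5.1.4 calls its effect on IL-6 poorly understood).
- *Samples diluted by replacement fluid.* At neutral balance that fluid replaces filtered plasma water. The returned blood is depleted of cleared solutes, not diluted overall.
- *An artefact that can never be told from a true fall.* At T72 oXiris has been off for about 24 h, so that value is free of its return stream, although ordinary CRRT may still be running.

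**Conclusion.** The point holds as a weakness in measuring secondary markers. The protocol leaves the site open for four of them, and one permitted site can under-read while a circuit returns cleared blood nearby. The effect would fall mainly on the oXiris arm, at T24 and T48, and in its favour. For a freely filtered solute it is roughly 1 to 9%, given an assumed 5 to 50% of return blood and a filtration fraction counted as all ultrafiltrate over inflow plus predilution. If the fraction is defined otherwise, about 17% is possible at the top of that range. For the mediators the size is unknown. A few percent is the likely order.

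Endotoxin activity at 72 hours, the primary endpoint, is arterial and is not touched. The change is worth making because these markers are meant to inform the design of later trials and it is almost free.

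**What to change.** In sections 7.8.2.2 and 7.8.2.3, specify the arterial line for all blood samples of IL-6, HMGB1, lactate and procalcitonin, in all three arms, drawn together with the endotoxin sample at Visits 2 to 5. Effluent samples stay as they are. State when the draw is made relative to circuit operation, the oXiris set change and the Toraymyxin session. Record any exception to the arterial site in the CRF, and bring the study-specific procedure of section 7.8.2.4 into line.

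The cost is a sentence or two in two sections and one CRF field. Arterial blood is already drawn for endotoxin at these visits, and section 7.8.2.5 foresees no extra puncture. The sample size is unchanged, and with arterial sampling the local return effect is zero in every arm.
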